# STANDARD CLINICAL PROTOCOL

[figure not shown]

**Standard Clinical Protocol.** Patients are randomized to standard care or cervical cooling at STAGE 2 of the protocol (yellow box). Physiological data (including ICP, brain oxymetry and L/P metabolic profile) is captured in digital format as per standard practice on our unit.

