## 2. OBJECTIVES

### 2.1 Primary Objective

**Safety.** Describe number and severity of complications associated with induction and maintenance of hypothermia using selective cervical cooling:

- failure to maintain the brain within target temperature;
- number of instances where external cooling blankets or ice-cold saline had to be used as a rescue strategy to achieve target temperature;
- duration and severity of cerebral hyperthermia;
- any other adverse event;

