## 3. STUDY DESIGN

This is a preliminary, proof-of-concept, randomised, interventional study.

The study will enrol at least 10 patients admitted to the Neurosciences and Trauma Critical Care Unit (NCCU, Addenbrooke's) following severe traumatic brain injury requiring invasive brain temperature monitoring and target temperature management as standard of care.

Brain temperature monitoring includes: ICP, brain oxymetry, microdialysis, haemodynamic variables. Physiological parameters and blood tests are also sampled on the ICM+ platform and local electronic medical record systems.

Randomisation of at least 10 patients will be made after the treating clinician has set a target temperature of 35°C. Using predetermined identical envelopes, patients will be assigned to two groups:

**Group 1, Standard Care (5 patients):** Medical and surgical management as per local treatment protocol (Figure). **Targeted temperature management induced by rapid infusion of ice-cold saline and maintained by automated cooling blankets.**

**Group 2, Experimental Care (5 patients):** Patients allocated to group 2 will receive the same treatment as those in group 1, with the exception of maintenance of **target temperature by using selective cervical cooling.**

Cervical cooling will be delivered with a purpose built prototype developed by Neuronguard. Brain temperature, core temperature (bladder or oesophageal), ICP and other physiological parameters will be continuously monitored and captured digitally as per standard local practice. Temperature targets are determined by the treating clinician, they will be recorded by a chart at the bedside, updated hourly, with brain temperature targets expressed as absolute values  $\pm 0.5^{\circ}\text{C}$ . Monitoring will continue for 48 hours, irrespective of temperature targets (i.e. to include rewarming, if indicated).

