### 5. SAFETY REPORTING

#### 5.1 Definition of Serious Adverse Events

A serious adverse event is any untoward medical occurrence that:

- Results in death,
- Is life-threatening,
- Requires inpatient hospitalisation or prolongation of existing hospitalisation,
- Results in persistent or significant disability/incapacity, or
- Other important medical events – in this cohort this would be uncontrollable intracranial hypertension

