#### 6.3 Analysis of Endpoints

Descriptive statistics will be used to report demographics and rate and nature of adverse events.

Non parametric tests will be used for between-group comparison of temperature data and paired data non parametric statistic tests for the brain/body differential temperature analysis.

Further exploratory data analysis of association between brain physiology, brain temperature, brain-body temperature gradients will be performed in the two groups to generate hypotheses for a larger clinical trial.

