## 7. ETHICAL AND REGULATORY COMPLIANCE

The main ethical challenge is around the issue of consent in comatose patients. Our group has extensive experience on the matter. Whenever possible, a “consultee” is identified and their opinion sought about the potential participant’s wishes and feelings in relation to the project, and whether he or she would have wanted to take part in the study. A member of the research team will approach the consultee to explain the study and its implications. Subjects are free to withdraw, or be withdrawn by their consultee if appropriate, at any point in the study, and they need not state a reason.

In regards to randomization, patients randomized to selective brain cooling using the Neuronguard prototype will be closely monitored and whenever target temperature cannot be achieved (or if there is any deterioration in brain physiology) the treating clinical will resort to systemic cooling, either by rapid infusion of ice cold saline or surface body cooling.

Participants in study group face the risk of lesions on the skin of the neck where cooling is applied. In order to minimize this risk we have created a controlled cooling system that senses the temperature of skin and adjust the heat extraction according to a pre-set level considered safe. The skin of the neck is checked by the research nurse each time the brain and core temperature are measured. In case any sign of lesion is present the treatment is immediately stopped.

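### Worsening brain physiology is treated as a hazard and recorded, but it enters the primary safety result only through adverse-event labelling, and rescue cooling for that reason falls outside the rescue count

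*Protocol*

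**What the plan says.** **Recording.** The caption to the Standard Clinical Protocol figure states: "Physiological data (including ICP, brain oxymetry and L/P metabolic profile) is captured in digital format as per standard practice on our unit". Section 3 adds that "ICP and other physiological parameters will be continuously monitored and captured digitally as per standard local practice", with monitoring for 48 hours whatever the temperature target.

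**Hazard.** Section 7 sends a device patient to systemic cooling if the target temperature cannot be reached, "or if there is any deterioration in brain physiology". The last item of the serious adverse event definition in section 5.1 reads: "Other important medical events – in this cohort this would be uncontrollable intracranial hypertension".

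**Objectives.** The primary safety objective (section 2.1, repeated in the Synopsis) has four items:
- failure to keep the brain within its target temperature;
- the number of times blankets or cold saline were needed as rescue to reach that target;
- "duration and severity of cerebral hyperthermia";
- a catch-all for other adverse events.

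The two secondary items in section 2.2 are the brain-to-core temperature difference and brain temperature within target.

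**Analysis.** Section 6.3 plans descriptive statistics for adverse events and non-parametric tests for temperature data. For brain physiology it plans only this, to generate hypotheses for a larger trial: "Further exploratory data analysis of association between brain physiology, brain temperature, brain-body temperature gradients will be performed in the two groups".

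**The concern.** Patients are randomised at Stage 2 of the unit's clinical protocol, and section 1 defends cooling as an option for intracranial hypertension that has not responded to first-level treatment. Control of ICP is thus close to the reason these patients are cooled, and loss of that control is a plausible way for a new cooling method to do harm.

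The primary objective is safety. It asks for duration and severity of hyperthermia but has no matching item for ICP or brain oxygenation. The planned association analysis asks whether physiology moves with temperature. It does not ask whether physiology was worse with the device than with standard care.

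According to section 6.1, the funding committee wanted safety and feasibility assessed before paying for a full-scale trial. A safety report with no by-arm description of ICP and brain oxygenation would leave that committee dependent on how individual changes were classified at the bedside, in a study for which the protocol describes no blinding.

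**Working it through.** The protocol gives no sample size or power derivation for this point, so there is no figure to reproduce. The check is to follow brain physiology through the text.

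**Step 1: coverage of the objectives.** Sections 2.1 and 2.2 list 4 + 2 = 6 items. Five concern temperature, counting rescue, which is tied to the temperature target. The sixth is the catch-all. None names ICP, oximetry or L/P.

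**Step 2: one case traced through.** Suppose a device patient's brain temperature stays within the ±0.5 °C band of section 3, ICP rises, and the clinician starts systemic cooling as section 7 allows.

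| Where it could be counted | Result on the wording |
|---|---|
| 2.1, failure to hold target | No |
| 2.1, rescue count | No, because rescue was not for temperature |
| 2.1, hyperthermia | No |
| 2.1, other adverse events | Only if someone labels it so |
| 5.1, serious adverse event | Only if a seriousness criterion is met |
| 6.3, physiology | Exploratory association only |

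If the clinician also lowers the target, the rescue might be counted as one for temperature. The wording leaves this open.

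**Step 3: when does the label apply?** Section 5.1 defines serious events only. Nothing states when a change in ICP, oximetry or L/P becomes an adverse event.

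**Step 4: the rescue wording.**
- Synopsis, Planned Sample Size: rescue if temperature targets are not achieved.
- Synopsis and section 2.1, Primary Objective: rescue counted when used to reach the target.
- Section 7: rescue for temperature or for deteriorating physiology.

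The first two give one reason and the third gives two.

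**Step 5: what data exist.** With 5 patients per arm and 48 hours each, 5 × 48 = 240 patient-hours per arm at most. This applies to ICP, which section 3 names as continuously monitored. Continuous capture of L/P is not stated, so the figure cannot be carried over to it.

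**Step 6: context on counts in five patients.** For an assumed true risk p per patient, the chance of no event is (1 − p)^5:
- p = 10%: 0.9^5 = 0.590
- p = 20%: 0.8^5 = 0.328
- p = 30%: 0.7^5 = 0.168

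The exact two-sided 95% upper limit for 0 of 5 is 1 − 0.025^(1/5) = 0.522. These figures hold for any yes/no event in five patients, and the risks are assumptions. They show that event counts carry little information here. They do not measure what is lost by leaving out ICP summaries.

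**The case against.** **The catch-all already covers it.** Non-serious deterioration can be recorded as an adverse event and is then reported under section 6.3. This stands. A reader might infer that worsening physiology short of the serious-event wording will go unreported; the text does not support that. It supports only that reporting depends on a label for which no criterion is given.

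**The serious-event definition does not limit the safety outcome.** Correct. Section 5.1 governs what counts as serious and section 5.2 what goes to the ethics committee. Reading the ICP wording in section 5.1 as the threshold for any adverse event would be wrong. That wording also concerns ICP alone; oximetry and L/P enter as hazards only through the broader phrase in section 7.

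**The rescue rule protects the patient.** A reader might picture device patients spending much longer with raised ICP while no event is shown. If the section 7 rule operates, time on the device during deterioration is cut short, so the documents do not support that picture. What remains is that such a rescue is itself a safety finding and, as worded, is not in the count.

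**Summaries belong in an analysis plan.** Table layouts and derived variables do, and a plan may exist that is not shown. Which variables make up the primary safety objective and which rescues count are fixed in this protocol, and section 6.3 expressly places physiology in the exploratory tier.

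**A pilot of ten cannot show a difference.** True, and no test is asked for.

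**Conclusion.** The point holds as a gap in the primary safety description and an inconsistency about rescue. The protocol treats worsening brain physiology as a hazard and records the relevant signals, but names them in none of its six objective items and uses them only in an association analysis that does not compare the arms. Non-serious deterioration reaches the safety result only through investigator labelling. Rescue for that reason is outside the count in section 2.1 on its plain wording, while section 7 allows it.

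The size is one of coverage: in the case traced above, no primary item is certain to record the event. No numerical bias can be derived. The conclusion rests on reading the rescue item in section 2.1 literally, and on no definition of a non-serious adverse event standing elsewhere in the trial's documents.

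This is an inexpensive improvement to a study whose primary objective is safety. It does not call the design into question.

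**What to change.** 1. In sections 2.1 and 6.3, add ICP, brain oximetry and L/P to the descriptive safety outcome. For each patient and by arm, over the 48-hour monitoring period from randomisation, report mean ICP, the proportion of monitored time above the ICP threshold already used in the unit's clinical protocol, and matching summaries of oximetry and L/P at the frequency at which they are recorded. Do no hypothesis test. The clinical protocol figure is not reproduced in the text available, so its threshold could not be checked, and none is proposed here.
2. Use all monitored time for the main summary. Device-arm values up to the first systemic rescue may be added, labelled as selectively truncated: deterioration can itself trigger the cut, and the control arm has no counterpart.
3. Count every systemic rescue and record its reason, temperature or physiology.
4. Reconcile the Synopsis, section 2.1 and section 7 on the reasons for rescue. Which clinical rule should apply is for the investigators.
5. Keep the association analysis as exploratory.

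**Cost.** Wording changes, a reason field for each rescue, and a few descriptive rows from data already captured; no extra patients or procedures. The rows will be imprecise at 5 versus 5 and may show the device less favourably.

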## 7. ETHICAL AND REGULATORY COMPLIANCE

The main ethical challenge is around the issue of consent in comatose patients. Our group has extensive experience on the matter. Whenever possible, a “consultee” is identified and their opinion sought about the potential participant’s wishes and feelings in relation to the project, and whether he or she would have wanted to take part in the study. A member of the research team will approach the consultee to explain the study and its implications. Subjects are free to withdraw, or be withdrawn by their consultee if appropriate, at any point in the study, and they need not state a reason.

In regards to randomization, patients randomized to selective brain cooling using the Neuronguard prototype will be closely monitored and whenever target temperature cannot be achieved (or if there is any deterioration in brain physiology) the treating clinical will resort to systemic cooling, either by rapid infusion of ice cold saline or surface body cooling.

Participants in study group face the risk of lesions on the skin of the neck where cooling is applied. In order to minimize this risk we have created a controlled cooling system that senses the temperature of skin and adjust the heat extraction according to a pre-set level considered safe. The skin of the neck is checked by the research nurse each time the brain and core temperature are measured. In case any sign of lesion is present the treatment is immediately stopped.

### 7.1 Data Protection and Patient Confidentiality

Data is collected and stored on the Trust safe server. Data exported from the Trust server will be anonymized and stored on encrypted computers. All audio/visual will contain no patient identifiable features. Pictures will be taken to document any adverse reaction connected to this new approach.

The data generated by the study will be analysed on NHS computers of the Cambridge University Hospital by the Principal Investigator and the appointed consultant of bio-statistics (if required). Physiological data will be anonymized and encrypted. Data will be stored in a firewall and password protected, secure NHS drive at the Addenbrooke's Hospital for a minimum of 6 years and possibly indefinitely in accordance with good research practice. Only the Principal Investigator will continue to have access to the data.

Cambridge University Hospital NHS Foundation Trust will keep identifiable information about participants for 5 years after the study has finished.

### 7.2 Indemnity

NHS indemnity scheme.

## 8. DISSEMINATION POLICY

The Principal investigator will produce a final study report and draft a paper for submission to a peer reviewed journal, acknowledging the founding bodies. The final study report will be circulated to all participants and clinical and research staff involved with the research. Raw data will be stored on the secure NHS server and owned by the University Department of Anaesthesia.

